### 2.3 Study design and data source

Routinely collected claims data from a large German statutory health insurance (BARMER) will be used to carry out the study. BARMER is the second largest statutory health insurance in Germany with about 8.6 million insured individuals (status of 2024). BARMER claims data are available on application for research purposes in anonymized data sets, hosted in a scientific data warehouse [in German: Wissenschaftliches Data Warehouse (WDWH)] by BARMER. Within the project VAC-MAC (in german: VACcinierung von MS/Arthritis/Colitis-Patient:innen, DRKS-ID: DRKS00031559, registered 28.08.2023), we have access to data from 2013 to 2021. VAC-MAC is a project funded by the German Innovations Fund (Innovationsfonds, grant number 01VSF21044) with multiple goals related to assessing and improving the vaccination coverage of individuals with MS, IBD, or CIRD.

The target population of all target trials consists of all individuals insured by the BARMER who fulfill the following inclusion criteria. The subject:

Has been enrolled in the BARMER health insurance company for at least 2 years before inclusion into the study with interruptions of no more than 5% of the total time.Is at least 18 years old at the start of observation.Has a biological sex of either male or female.Did not receive an organ transplantation in the last 2 years before inclusion into the study.Did not have any form of cancer in the last 2 years before inclusion into the study.Did not have an autoimmune-related disease other than MS, IBD, or CIRD in the last 2 years before inclusion into the study.

The start of the observation period/study is defined as the date on which an individual is included in the study during the trial emulation, as outlined in Section 2.6. In addition to these criteria, we also define one trial-specific inclusion criteria for each vaccine-effectiveness analysis. For the herpes zoster vaccine-effectiveness study, we require that the individual has not previously received a herpes zoster vaccination. Similarly, for the influenza vaccine-effectiveness trials, we require that the individual has not already received an influenza vaccination in the current influenza season.

A detailed list of all International Statistical Classification of Diseases and Related Health Problems (ICD)-10 Codes used to assess the inclusion criteria is given in the online supplement. We require two years of previous enrolment in the BARMER because we would otherwise be unable to obtain information on all relevant confounders as described in Section 2.5.4. In these 2 years of enrolment, small interruptions are allowed (up to 5% of the total time), as a compromise between the potential for misclassification that arises, because no information is recorded when a person is not insured at BARMER, and the available sample size. The studies are further constrained to contain only biological males and females due to small amounts and inconsistent coding of the “diverse” category in the BARMER data. People with cancer, previous organ transplantations and other autoimmune diseases are excluded due to the effect these conditions and/or their treatment have on the immune system. There are no other exclusion criteria in this study. Special populations, such as pregnant women and people with other chronic or life-threatening diseases are also eligible to be included in the study.

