**Health status**	
The general health status of an individual. This includes both physical and psychological wellbeing.	Two indicators will be used as proxies for this variable. We will consider: (1) A modified version of the Charlson comorbidity index (81) that does not include the main diseases of interest in this study, calculated using ICD codes from the last year. (2) The number of inpatient hospital stays in the last 2 years. (3) The current official level of care.

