**Influenza immunity**	
Whether the individual already has acquired some immunity against influenza through previous influenza vaccinations or a previous influenza infection.	We will consider: (1) Whether the individual has received an influenza vaccination in the previous year. (2) Whether the individual has experienced an influenza infection in the previous year.

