**Vaccination plan**	
For individuals with MS, IBD, or CIRD it is not unusual that the vaccination is planned in advance by the physician and aligned with changes in medication that may have immunosuppressive effects. For example, the physician may decide that the individual should be vaccinated next week. To allow the patients immune system to make a proper response to the vaccination, a new prescription of immunosuppressive medication is then delayed for a few weeks. This variable states whether such a plan was made or not.	An indicator of whether a person receives a medication change shortly after vaccination may be created. However, this type of indicator breaks the time-line, since information from the future would be used. We will perform an additional sensitivity analysis to determine the effect of using this indicator as an adjustment variable.

Using this DAG and the *backdoor criterion* (47), we then identified separate sets of factors that we need to adjust for in each vaccine effectiveness analysis (53). These sufficient adjustment sets are very similar. In both of the two considered analyses, we will adjust for *Age, Sex, Place, Calender Time, Cautiousness, Disease Status, Healthcare-Seeking Behavior* (HSB), *Treatment, Health Status*, and *Vaccination Plan*. The only differences are that we additionally have to adjust for *Chicken Pox* and *Herpes Zoster Immunity* in the herpes zoster vaccine effectiveness analysis and that we also have to adjust for *Influenza Immunity* in the influenza vaccine effectiveness analysis.

Note that, given our assumptions, there is no need to adjust for socioeconomic status in either analysis, because we hypothesize that the effect of this variable on each outcome is only indirect and is thus already adjusted for by including the other variables. It is also not strictly necessary to adjust for sex in the influenza vaccine effectiveness analysis for the same reason. We choose to include sex anyway, because it can be seen as a proxy for other relevant confounders such as cautiousness that we may not be able to fully adjust for given the mentioned indicators (48).

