#### 2.6.1 Matching method

Due to the different target trials per vaccine of interest, the planned matching and analysis strategy also differs slightly. To analyze the effectiveness of the herpes zoster vaccine, a single matching process will be used. For the influenza vaccine effectiveness trials we will use the same procedure, with the only difference being that it will be performed separately for each influenza season. The matching will be carried out as follows.

For the previously defined start date of the respective trial, the eligibility of all individuals contained in the BARMER database will be determined using the above mentioned inclusion criteria. Eligibility will be checked using only the information available at that time. Every individual who was vaccinated with the vaccine of interest on this date is subsequently included in the dataset, in the treatment group. For every individual included in this way, we then include *k* further individuals who fulfill the inclusion criteria, but have not been vaccinated yet, in the control group. These controls will be matched exactly by age in years, gender, place of residence and disease group. If more than *k* potential controls are identified for a case, *k* controls will be picked at random from these. We will try to include 2 controls per case first (*k* = 2), but will lower this number to 1 if the number of available matches is insufficient. The date of inclusion equals “time zero” (27) for all individuals. Information about all relevant confounders is recorded as available on this date, corresponding to baseline information. This procedure is repeated on all subsequent days, until the emulated trial is over.

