by disease status, where *t* denotes the point in time and *RR*(*t*) is the relative risk of experiencing the respective outcome at time *t* in the vaccinated vs. unvaccinated group. Formal contrasts of the disease specific vaccine effectiveness estimates will then also be calculated. Cluster-robust standard errors will be used in the Cox model to adjust for potential dependencies introduced by matching (63). Non-parametric bootstrapping will be used to derive confidence intervals for the vaccine effectiveness and their formal comparisons. Although Abadie and Imbens (64) demonstrated analytically that bootstrapping is not a valid strategy to estimate standard errors in matched samples, it has been shown to work well in simulation studies (65). Due to these simulation results and a lack of alternatives we will therefore still rely on this method.

A very similar analysis strategy will be used to assess the moderating effect of the prior use of immunosuppressive medication on the vaccine effectiveness. In this analysis, only individuals with MS, IBD, or CIRD will be included. The entire analysis described above is then repeated, stratified by disease group and the severity of the received immunosuppresive medication (if any). Additionally, g-computation will be used to estimate the age-specific vaccine-effectiveness in each trial. To obtain a single estimate for the influenza vaccine, we will also use standard meta-analytic approaches to combine the estimates obtained from each of the four emulated influenza trials.

The proportional hazards assumption will be checked using Schoenfeld residual plots (66). If the assumption is deemed violated, we will try different strategies, such as inclusion of time-dependent hazard-ratios and variable transformations, to alleviate this issue. If these methods are unsuccessful, other models such as the additive hazards model (67) with a similar specification will be employed instead. In addition, we will perform a sensitivity analysis in which we will use a weighted Kaplan-Meier estimator instead of g-computation (68), where the weights will be estimated using entropy balancing (69).

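### Pregnant women stay eligible, but pregnancy is neither matched nor adjusted for, so influenza VE in women of child-bearing age may keep residual confounding

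*Protocol article*

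**What the plan says.** All references are to the protocol article.

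- **Eligibility (Section 2.3).** After the inclusion criteria, the article says there are no further exclusions and adds: "Special populations, such as pregnant women and people with other chronic or life-threatening diseases are also eligible to be included in the study".
- **Matching (Section 2.6.1).** "These controls will be matched exactly by age in years, gender, place of residence and disease group", on the day the vaccinated person enters.
- **Adjustment set (Section 2.5.4).** For both vaccines, "we will adjust for *Age, Sex, Place, Calender Time, Cautiousness, Disease Status, Healthcare-Seeking Behavior* (HSB), *Treatment, Health Status*, and *Vaccination Plan". The influenza analysis adds only influenza immunity, which has two indicators: "Whether the individual has received an influenza vaccination in the previous year", and infection in the previous year.
- **Health status (Table 2).** "Two indicators will be used as proxies for this variable", although three follow: "A modified version of the Charlson comorbidity index (81) that does not include the main diseases of interest in this study", the number of inpatient stays in two years, and the official level of care.
- **Healthcare-seeking behaviour (Table 2).** Primary care visits, all physician visits, pneumococcal vaccination and a preventive check-up.
- **Where it would show (Section 2.6.2).** "g-computation will be used to estimate the age-specific vaccine-effectiveness in each trial".

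Pregnancy is mentioned once, in the eligibility statement.

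**The concern.** The article singles out pregnant women as a special population and includes them, yet gives the analysis no means of telling them apart. Matching on age and sex does not separate pregnant from non-pregnant women, so a pregnant vaccinee will often be paired with a non-pregnant control.

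This matters only if pregnancy is related both to being vaccinated and to the outcome. Both links are plausible for influenza. The primary influenza outcome (Section 2.5.3) requires contact with a health care professional, so it depends on the threshold for seeking care as well as on infection. Pregnancy could shift that threshold, and it could shift vaccine uptake.

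Any resulting bias would sit in one age-sex band. It would therefore be least diluted in the age-specific influenza VE, which is a planned output of every influenza trial.

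**Working it through.** **Step 1: is pregnancy captured anywhere?** Age, sex, place, calendar time and disease status do not capture it. Visit counts and inpatient stays respond to pregnancy, but they look back one and two years, mix antenatal care with illness, and hold little trace of an early pregnancy. Treatment category covers the last year and may reflect drugs used before the pregnancy. Influenza immunity is unrelated. These are partial proxies at best. Table 2 sends the detail of the treatment variable to the online supplement, but it lists the indicators for health status and healthcare-seeking in full.

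**Step 2: how large could the bias be?** The article states no figure to reproduce, so every value below is an assumption. For one binary confounder whose effect on risk is the same in vaccinated and unvaccinated:

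factor = [1 + p_v(RR − 1)] / [1 + p_c(RR − 1)], and VE read = 1 − (1 − true VE) × factor

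Here p_v and p_c are the shares pregnant among vaccinated and control women of child-bearing age. RR is the relative risk of medically attended influenza with pregnancy that remains after the planned adjustment.

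True VE 50%:

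| p_v | p_c | RR | Factor | VE read |
|---|---|---|---|---|
| 6% | 3% | 1.5 | 1.030/1.015 = 1.015 | 49.3% |
| 15% | 4% | 2 | 1.150/1.040 = 1.106 | 44.7% |
| 15% | 4% | 0.7 | 0.955/0.988 = 0.967 | 51.7% |

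**Step 3: a second set of assumptions.** True VE 40%, with p_v derived from p_c through a pregnancy-vaccination odds ratio (OR): odds_v = OR × p_c/(1 − p_c), p_v = odds_v/(1 + odds_v).

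- Middle case (p_c 4%, OR 2, RR 2): p_v = 7.7%, factor 1.077/1.040 = 1.036, VE read 37.9%.
- Upper extreme (p_c 6%, OR 4, RR 3): p_v = 20.3%, factor 1.407/1.120 = 1.256, VE read 24.6%.
- Opposite direction (p_c 6%, OR 4, RR 0.7): factor 0.939/0.982 = 0.956, VE read 42.6%.
- OR = 1 or RR = 1: factor 1, no bias.

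**Step 4: all-ages VE.** If these women supply an assumed share s of the total, the overall factor is about 1 + s(factor − 1). With a stratum factor as high as 1.25 and true VE 40%:

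- s = 5%: factor 1.0125, VE 39.25%.
- s = 15%: factor 1.0375, VE 37.75%.

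**Step 5: disease contrast (ratio of VEs).** Take a whole disease group with 2-3% of vaccinees and 1% of controls pregnant, RR 1.5-2 and true VE 50%.

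- The factors are 1.010/1.005 = 1.005 and 1.03/1.01 = 1.020, so VE reads 49.8% and 49.0%.
- Against an unbiased comparison group also at 50%, the VE ratio is 0.995 to 0.980 instead of 1.

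Within the stratum, with true VE 40% in both groups:

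- A common factor leaves the ratio at 1.00.
- Factors of 1.10 (diseased) and 1.04 (non-diseased) give (1 − 0.66)/(1 − 0.624) = 0.340/0.376 = 0.90.

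If the true VEs differ, a common factor also moves the ratio slightly, because VE is one minus a relative risk. With 40% and 50% and a common factor of 1.02, it is 0.388/0.490 = 0.792 instead of 0.800. That changes the size of a real difference and does not create one.

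**The case against.** **The confounding is not demonstrated.** A reader might infer that influenza VE in these women is certainly confounded. The documents do not support that. They state neither that pregnancy changes vaccination nor that it changes medically attended influenza, and both links must survive the planned adjustment. If either is absent, the bias is zero, and its direction is open. This objection stands.

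**The figures ignore the partial proxies.** Visit counts, inpatient stays and treatment category will absorb part of any pregnancy effect, so an RR of 1.5-2 treated as fully residual is on the high side. This stands too, and it makes the lower end of the range more credible than the upper.

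**The plan admits residual confounding.** Sections 2.5.4, 2.6.5 and 3 concede an imperfect adjustment set and possible unknown confounders, and Section 2.6.6 adds urinary tract infection as a negative control outcome. This helps only in part. Pregnancy is known to the authors, since Section 2.3 names it, but it is not among the limitations they discuss. A general negative control neither identifies nor removes a confounder confined to one age-sex band.

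**Disease groups.** A reader might infer that disease groups with more young women are especially biased. The article gives counts of patients by disease but no age or sex distribution, so this has no support.

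**Care homes.** A reader might raise the same point for care-home residents. Level of care is already an adjustment variable, and the lack of household and contact information is disclosed and discussed. This would largely restate a declared limitation.

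**Conclusion.** The omission is real and can be read directly from the text: an expressly eligible group has no matching variable, adjustment concept or indicator. What follows is possible, not established, residual confounding of influenza VE in women of child-bearing age.

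Under the first set of assumptions the distortion there is roughly one to five VE points downward from 50%, with an upward shift if the residual relative risk is below 1. Only extreme assumptions give about 15 points (24.6% against a true 40%). All-ages VE and the disease contrast are likely to move little, and an apparent disease difference where none exists requires the bias to differ by disease status.

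The point therefore bears mainly on the age-specific influenza results. It is a low-cost improvement to a fixed adjustment set and does not threaten the main conclusions.

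**What to change.** For the influenza trials:

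1. Define a binary indicator of pregnancy at time zero using only claims known by then. Suitable sources are exactly dated antenatal services and inpatient diagnoses. Outpatient diagnoses should count only from quarters completed before time zero, because Section 2.5.3 says they carry an interval of up to 91 days. Delivery codes after time zero should not be used, since they bring in future information.
2. Add the indicator to the Cox/g-computation covariates and to the entropy-balancing weights of the weighted Kaplan-Meier sensitivity analysis (Section 2.6.2).
3. Run a sensitivity analysis that excludes women identified as pregnant at time zero.

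Exact matching on pregnancy is not advised. Section 2.6.1 rules out richer matching methods on computational grounds and loosens the matching once more than 10% of vaccinees are unmatched, so another exact factor would work against both limits.

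The cost is one extra covariate and one sensitivity analysis. This assumes that the claims already held include dated antenatal services, which the article does not state. Some early pregnancies will be missed, so the adjustment will reduce any bias but not remove all of it.

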### 2.4 Study period

Although information between 2013 and 2021 is available, we will not use this entire duration as a study period for all of the target trial emulations. First, as described in Section 2.2, there will be one trial emulation per influenza season, with only the time during the respective season being included. Secondly, the first influenza vaccine effectiveness trial emulation will start with the influenza season of 2015/2016 and not with influenza season of 2013/2014, because we need two years of previous follow-up to determine eligibility of the individual and to measure the relevant confounders. Finally, although information for a fifth trial emulation in the influenza season of 2019/2020 would be available, we will not perform this analysis. The reason for this decision is that the COVID-19 pandemic started during this season and largely overshadowed the influenza season of this year. The likely large amounts of underreporting of influenza infections during the COVID-19 pandemic, combined with the actual effects of the pandemic and the measures taken to combat it (33), make a target trial emulation infeasible. Similarly, the target trial for the herpes zoster vaccine effectiveness analysis only starts on the 01.12.2018, because the inactivated herpes zoster vaccine was not available in Germany and not recommended by the STIKO (in German: “Ständige Impfkommission”) before this date (29).

